## Abstract

**Background:**

Prophylactic abdominal drainage is current standard practice after distal pancreatectomy (DP), with the aim to divert pancreatic fluid in case of a postoperative pancreatic fistula (POPF) aimed to prevent further complications as bleeding. Whereas POPF after pancreatoduodenectomy, by definition, involves infection due to anastomotic dehiscence, a POPF after DP is essentially sterile since the bowel is not opened and no anastomoses are created. Routine drainage after DP could potentially be omitted and this could even be beneficial because of the hypothetical prevention of drain-induced infections (Fisher, Surgery 52:205–22, 2018). Abdominal drainage, moreover, should only be performed if it provides additional safety or comfort to the patient. In clinical practice, drains cause clear discomfort. One multicenter randomized controlled trial confirmed the safety of omitting abdominal drainage but did not stratify patients according to their risk of POPF and did not describe a standardized strategy for pancreatic transection. Therefore, a large pragmatic multicenter randomized controlled trial is required, with prespecified POPF risk groups and a homogeneous method of stump closure.

The objective of the PANDORINA trial is to evaluate the non-inferiority of omitting routine intra-abdominal drainage after DP on postoperative morbidity (Clavien-Dindo score ≥ 3), and, secondarily, POPF grade B/C.

**Methods/design:**

Binational multicenter randomized controlled non-inferiority trial, stratifying patients to high and low risk for POPF grade B/C and incorporating a standardized strategy for pancreatic transection. Two groups of 141 patients (282 in total) undergoing elective DP (either open or minimally invasive, with or without splenectomy). Primary outcome is postoperative rate of morbidity (Clavien-Dindo score ≥ 3), and the most relevant secondary outcome is grade B/C POPF. Other secondary outcomes include surgical reintervention, percutaneous catheter drainage, endoscopic catheter drainage, abdominal collections (not requiring drainage), wound infection, delayed gastric emptying, postpancreatectomy hemorrhage as defined by the international study group for pancreatic surgery (ISGPS) (Wente et al., Surgery 142:20–5, 2007), length of stay (LOS), readmission within 90 days, in-hospital mortality, and 90-day mortality.

**Discussion:**

PANDORINA is the first binational, multicenter, randomized controlled non-inferiority trial with the primary objective to evaluate the hypothesis that omitting prophylactic abdominal drainage after DP does not worsen the risk of postoperative severe complications (Wente etal., Surgery 142:20–5, 2007; Bassi et al., Surgery 161:584–91, 2017). Most of the published studies on drain placement after pancreatectomy focus on both pancreatoduodenectomy and DP, but these two entities present are associated with different complications and therefore deserve separate evaluation (McMillan et al., Surgery 159:1013–22, 2016; Pratt et al., J Gastrointest Surg 10:1264–78, 2006). The PANDORINA trial is innovative since it takes the preoperative risk on POPF into account based on the D-FRS and it warrants homogenous stump closing by using the same graded compression technique and same stapling device (de Pastena et al., Ann Surg 2022; [name] and Stauffer, Surg Endosc 25:2643–9, 2011).

**Supplementary Information:**

The online version contains supplementary material available at 10.1186/s13063-022-06736-5.

## Background

### Clinical background

The debate on routine prophylactic abdominal drainage after partial pancreatectomy has been ongoing for decades [1, 2]. Most series combine outcomes of pancreatoduodenectomy and distal pancreatectomy (DP) or focus on pancreatoduodenectomy only. There is, however, an essential difference between POPF in DP and pancreatoduodenectomy. Whereas POPF after pancreatoduodenectomy, by definition, involves infection due to anastomotic dehiscence between pancreas and small bowel, a POPF after DP is, by definition, initially sterile since no anastomoses are created. Prophylactic abdominal drainage after DP could therefore also introduce bacteria and cause drain-induced infections [3].

Recent reviews underline the need of data regarding abdominal drainage in DP [4–6]. In high-volume centers, DP has a very low mortality (0–2%) but the morbidity rate remains high (24 to 56%) with postoperative pancreatic fistula (POPF) as most common complication (0% to 61%) and cause of further complications [7–14]. Unfortunately, the risk of POPF after DP has proven difficult to predict [15]. Prophylactic abdominal drainage after DP allows for evacuation of pancreatic fluid, in case of POPF, but a drain could theoretically also induce infection, especially when left in place for prolonged periods [6, 16] or even bleeding due to vascular erosion [1]. In patients with a leak at the pancreatic transection margin, without a drain, a sterile and asymptomatic pseudocyst (i.e., no infected collection requiring no intervention) could occur [17].

A randomized controlled trial (RCT) is mandatory to determine whether patients are better off without the use of prophylactic abdominal drainage after DP.

### Need for a randomized trial

Current published series on prophylactic abdominal drainage after DP are mostly retrospective, only one multicenter randomized trial is available and this did not stratify patients according to their risk of POPF and did not use a standardized technique of transecting the pancreas [2]. It could be that outcomes of prophylactic abdominal drainage differ between patients with low and high risk of POPF after DP.

PANDORINA is a binational multicenter, randomized controlled non-inferiority trial with the primary objective to evaluate the hypothesis that omitting prophylactic abdominal drainage after DP does not worsen the risk of postoperative Clavien-Dindo score ≥ 3 complications (e.g., reinterventions, catheter drainage, wound infections, postoperative pancreatic hemorrhage, feeding tube placement) [18, 19].

## Methods

### Study design

Patients undergoing elective DP will be randomly allocated in a 1:1 ratio to no prophylactic abdominal drainage or prophylactic abdominal drainage after surgery, stratified based on the risk of POPF. This protocol was developed according to the SPIRIT guidelines [20]. Total inclusion time of the study is planned to be 24 months from start of recruitment and the total study time 36 months. The study structure includes setup of sites (4–6 months), enrollment (24–30 months), and data analysis and reporting results (4 months).

In case of readmission related to surgery within 90 days after initial discharge, follow-up for secondary outcomes will be extended to the entire duration of readmission.

### Study population

Adult patients with an indication for elective DP, with or without splenectomy, minimally invasive or open, for any indication.

### Inclusion criteria

In order to be eligible to participate to the study, a patient must meet all of the following criteria:° At least 18 years old;° Elective indication for DP, with or without splenectomy, minimally invasive or open, with and without sparing of splenic vessels, for all indications;° Fit to undergo surgery;° Oral and written informed consent.

### Exclusion criteria

Patients who meet any of the following criteria will be excluded from participation in this study:° Pregnancy;° DP as a secondary procedure during gastric or colonic resection;° Colonic resection required for cancer extension (gastric resection allowed);° Additional hepatic resection;° Participation to another study with interference with study outcome;° ASA 4 / WHO 3;° Arterial resection other than splenic artery.

### Indications for DP

Numerous indications for elective DP exist, and the most common indications are as follows: ductal adenocarcinoma, mucinous cystic neoplasm, intraductal papillary mucinous neoplasm, neuroendocrine tumor, solid-pseudopapillary neoplasms, chronic pancreatitis. All indications are included in this trial.

### Sample size calculation

The PANDORINA trial is as a non-inferiority randomized trial, hypothesizing that the outcome (i.e., postoperative complications Clavien-Dindo score ≥ 3 and, secondarily, clinically relevant POPF, grades B and C) in patients undergoing DP without prophylactic abdominal drainage are non-inferior to those of patients with routine prophylactic abdominal drainage after surgery. The sample size is calculated according to the formula (available at https://www.sealedenvelope.com/power/binary-noninferior/):$$n=f\left(\alpha, \beta \right)\times \left[{\pi}_{\mathrm{s}}\times \left(100-{\pi}_{\mathrm{s}}\right)+{\pi}_{\mathrm{e}}\times \left(100-{\pi}_{\mathrm{e}}\right)\right]/{\left({\pi}_{\mathrm{s}}-{\pi}_{\mathrm{e}}-d\right)}^2$$ where *π*_s_ and *π*_e_ are the true percent “success” in the “drain” and “no drain” groups respectively.$$F\left(\alpha, \beta \right)={\left[{\varPhi}^{-1}\left(\alpha \right)+{\varPhi}^{-1}\left(\beta \right)\right]}^2$$

And *φ*^−1^ is the cumulative distribution function of a standardized normal deviate.

Patients recruited in the PANDORINA trial will be randomized within the referred Institute with a 1:1 allocation ratio. The primary endpoint of the present trial is the rate of Clavien-Dindo ≥3 major complications, following the assumption: 2.5% one-sided significance level (*α*), 80% power (1−*β*), and a non-inferiority level of 8%. The expected success percentage in the intervention arm (no prophylactic abdominal drainage) of 77% and a success percentage in the control group of 70% (prophylactic abdominal drainage, based on the multicenter LEOPARD trial with a majority of minimally invasive procedures) [21]. The needed number of patients was calculated with a sealed envelope: a total of 272 patients are required. Including a 3% of possible drop-out after randomization, the total required sample size is 282 patients (141 patients per arm).

The most relevant secondary endpoint is the rate of clinically relevant POPF (grades B and C). The sample size was calculated with the following assumption: 2.5% one-sided significance level (*α*), 80% power (1−*β*), and a non-inferiority level of 8%. The expected success percentage in the intervention arm (no prophylactic abdominal drainage) is 81%, and a success percentage in the control group (prophylactic abdominal drainage) is 75%. This difference of 6% less grade B/C POPF without abdominal drainage is based on the Van Buren trial, and the baseline risk of 25% grade B/C POPF is based on the recently published distal fistula risk score (D-FRS), a combined Dutch/Verona multicenter study [22]. The needed number of patients was calculated with sealed envelope: a total of 274 patients. Including a 3% of possible drop-out after randomization, the total required sample size is 282 patients (141 patients per arm).

Based on the second (slightly lager) sample size calculation, we will include 282 patients so that conclusions can be drawn for both endpoints.

### Stratification

The patients included in the present trial will be stratified in preoperative estimated high and low risk for grade B/C POPF. High-risk patients is defined as a pancreatic duct diameter > 3 mm and/or pancreatic height (at the neck) > 19 mm based on the D-FRS [22]. Other patients are considered as low risk. Patients will also be stratified based on annual hospital volume of DP. Stratification will be as follows: high volume > 40 DPs annual and low volume will be ≤ 39 DPs annual.

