### Randomization and treatment allocation

Eligible patients for the study will be identified at the outpatient clinic and in this stage informed consent will be obtained; the randomization will take place directly after start of the operation, when the decision is made to proceed with the resection. The surgeon performing the operation will call the study coordinator to perform the randomization in Castor EDC. Patients will be analyzed according to the allocated treatment, as per intention-to-treat principles. If during the operation is chosen not to act conform the randomization, specification of this choice is required. A per-protocol analysis will also be performed for the primary endpoint.

A data safety monitoring committee will assess safety endpoints per 50 randomized patients. All patients will be randomized centrally using an online computer-controlled permuted-block randomization module in a 1:1 ratio. The block sizes itself will be subject to random variation with block sizes varying from 4 to 8 patients. The entire randomization will be concealed to all involved investigators except the trial coordinators. Patients will be coded by a numeric randomization code and the principal investigator will be the only one with access to it and investigators and patients are not blinded. Patients will be stratified according to high or low risk and minimally invasive and open procedure. The source data will be stored digitally and will be kept by the project leader for 15 years after the inclusion of the last patient.

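### The Stratification section and the Randomization section name different second stratification factors, and the volume classes leave exactly 40 procedures a year unassigned

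*Protocol article*

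**What the plan says.** Two sections of the protocol article set out the strata.

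- **Stratification.** Patients "will be stratified in preoperative estimated high and low risk for grade B/C POPF". A second factor follows: "Patients will also be stratified based on annual hospital volume of DP". Its classes are "high volume > 40 DPs annual and low volume will be ≤ 39 DPs annual". Surgical approach is not mentioned.
- **Randomization and treatment allocation.** "Patients will be stratified according to high or low risk and minimally invasive and open procedure". Neither hospital volume nor centre is mentioned. The same section describes central 1:1 allocation by permuted blocks of varying size, 4 to 8.

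Three other places touch on the scheme. The abstract speaks of "stratifying patients to high and low risk for POPF grade B/C" and the Study design section says "stratified based on the risk of POPF". The Sample size calculation section says patients will be "randomized within the referred Institute with a 1:1 allocation ratio".

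The Statistical analysis section gives a chi-square test for the primary non-inferiority comparison and does not mention strata. It defers detail to an analysis plan to be drafted before database lock. The Trial status section reports 152 of 282 patients randomised when the article was submitted.

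**The concern.** Stratification factors are fixed when the first patient is randomised, so an analysis plan written later cannot decide what they were. The article does not leave the factors out. It states them twice, with a different second factor each time. A statistician working from this text could not tell whether the module balanced the arms on hospital volume, on approach, or on both.

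Two things are at stake. First, an analysis that respects the randomisation has to use the factors actually programmed. If the choice between volume and approach is left open until outcomes are known, an avoidable discretionary choice remains in a trial where investigators and patients are not blinded. Second, the article presents risk stratification as an advance over the earlier multicentre trial of drain omission, so the scheme should be recoverable from its own text.

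The gap at 40 is a smaller, separate defect. As written, the rule gives no stratum to a centre with that volume.

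**Working it through.** **1. The two defining sections side by side**

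| Section | Factor 1 | Factor 2 |
|---|---|---|
| Stratification | POPF risk, high or low | Annual hospital volume |
| Randomization and treatment allocation | POPF risk, high or low | Minimally invasive or open |

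**2. What each possible live scheme implies**

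- Risk × volume is programmed: the Randomization section names a wrong factor and omits a right one.
- Risk × approach is programmed: the same is true of the Stratification section.
- Risk × volume × approach is programmed: each section omits one factor.
- Anything else is programmed: both sections are wrong.

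In every case at least one section has to change.

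**3. The volume rule**

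The Quality section requires at least 10 DPs a year. Testing every whole number from 10 to 79 against the two conditions (over 40; 39 or fewer), the only value that meets neither is 40.

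**4. Cell sizes under the factors the two sections name, at N = 282**

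- Risk × volume: 2 × 2 = 4 cells, 282 / 4 = 70.5 patients per cell on average.
- Risk × approach: 2 × 2 = 4 cells, 70.5 per cell.
- All three: 2 × 2 × 2 = 8 cells, 282 / 8 = 35.25 per cell.

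These are means and real cells will be uneven. Against blocks of 4 to 8 they show no general difficulty in filling blocks.

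**5. Sample size**

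Per arm, n = (z₀.₉₇₅ + z₀.₈₀)² × [p₁(1 − p₁) + p₂(1 − p₂)] / (margin + p₂ − p₁)², where p₁ is the drain arm and p₂ the no-drain arm. Inputs are from the Sample size calculation section.

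- Primary endpoint (70% and 77% success, margin 8 points): 7.849 × (0.2100 + 0.1771) / 0.15² = 135.04, so 136 per arm and 272 in total, as stated.
- Grade B/C POPF (75% and 81%, same margin): 7.849 × (0.1875 + 0.1539) / 0.14² = 136.7, so 137 per arm and 274 in total, as stated.

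No stratification term enters the formula, so the inconsistency leaves these figures unchanged.

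**The case against.** The strongest defence is that the two sections are partial lists, not rival schemes. Neither says it is exhaustive, and the Stratification section introduces volume as an addition. Combined, they give risk × volume × approach. That is possible, but no section states that scheme, and on this reading both sections are still incomplete.

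A second defence is that no analysis harm is shown. The stated primary test uses no strata, so no adjustment factor in the text can conflict with the randomisation. Allocation is central, 1:1 and blocked under either list. Which factors enter the primary model is often left to the analysis plan. This stands to a large extent: no bias in the treatment comparison is shown, and silence on strata in the analysis is not by itself an error. It does not rescue the factor list, which the protocol has to get right.

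The gap at 40 is probably a typing slip, and no centre's volume is reported, so no affected centre is shown.

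A reader might infer two stronger claims that the documents do not support.

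- *That four incompatible schemes are described.* The abstract and Study design lines are short summaries that hold under any scheme containing POPF risk; neither says risk alone. The phrase about randomising within the institute is not called stratification and may only say where randomisation happens. A centre stratum would also make a volume stratum redundant, because volume is a property of the centre.
- *That crossing centre with the other factors leaves cells too sparse for the blocks.* No section states such a scheme. The article says sixteen Dutch centres are invited, but gives neither the number participating nor the number of Italian sites.

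**Conclusion.** The point holds as an internal inconsistency and should be fixed. The two sections that define the strata disagree on the second factor, nothing in the article resolves it, and the volume classes miss exactly one value, 40. Because 152 of 282 patients (54%) had been randomised at submission, a scheme was already in use and at least one section misdescribes it or lists it incompletely. This assumes that the module's settings did not change during recruitment; the article reports no change.

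The consequence is limited. Sample size is unaffected, the two lists and their combination give 4 or 8 cells that the blocks can fill, and no bias is demonstrated. What is lost is a determinable allocation rule and, with it, a fixed set of strata for the primary comparison.

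**What to change.** 1. Check which factors and classes are programmed in Castor EDC. If they changed during recruitment, record each set with its dates.
2. State those factors once, and align the Stratification section and the Randomization section to them.
3. If volume is a factor, write the two classes so that they meet, with 40 placed as the module places it. If volume is not a factor, remove the volume rule.
4. In the Sample size calculation section, say whether randomising within the institute means a centre stratum. If it does not, reword it.
5. Use the programmed factors as strata in the primary non-inferiority comparison, for example a stratified risk difference with its 95% confidence interval set against the 8-point margin, in place of the unstratified chi-square test. Fix this in the analysis plan before database lock.

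The cost is a check of the live settings, a text correction and a line in the analysis plan. No extra patients and no change to the allocation are needed.

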### Quality

Participating centers should perform at least 10 DPs per year for any diagnosis. Surgeons should have performed > 50 pancreatic resections (any type, any diagnosis) in the past 5 years and > 20 DPs for any diagnosis ever. All sixteen centers participating in the Dutch Pancreatic Cancer Group are invited.

## Treatment of subjects

### Investigation treatment

#### Work-up

Preoperative work-up is according to routine practice.

#### Surgical technique

Agreement was reached regarding the surgical technique standards that should be followed during both open and minimally invasive DP. The following highlights are allowed as long as the same technique is applied both in the intervention and control group:Transection of the pancreas will be performed with a stapler* using the commonly used gradual stepwise compression technique (i.e., 4–5 min to close the stapler to prevent (micro-)rupture of the pancreas), as described by [name] et al. [17], in both open and minimally invasive surgery. In all patients, graded compression technique is used as described by [name] et al. with the same type of stapler. [name] was a senior advisor in the design of this current study.In case of a soft pancreas with transection at the pancreatic neck, a white (vascular) or blue stapler filling is used; in case of a fibrotic thick pancreas, a green stapler filling is used.Use of co-interventions for pancreatic stump closure is not advised. If they are used, such as human fibrinogen/thrombin sealant, fibrin-like glues, bio-absorbable reinforcement, autologous patches, and suture closure, they should be used routinely in all patients undergoing DP (i.e., in both arms of the trial) in that particular center;Preoperative endoscopic injection of botulinum toxin into the Sphincter of Oddi to prevent postoperative pancreatic fistula after DP is not advised. If used, this is not an exclusion criteria as long as it is used routinely in all patients undergoing DP (i.e., in both arms of the trial) in that particular center [23, 24].◦ *During the trial, one type of stapler is used (Ethicon®) to reduce heterogeneity.

#### Somatostatin analogs

Use of somatostatin analogs (e.g., Pasireotide®) is not advised. If used, this is not an exclusion criteria as long as it is used routinely in all patients undergoing DP (i.e., in both arms of the trial) in that particular center [25].

#### Prophylactic abdominal drainage

In the control arm, the abdominal drain will be placed intraoperatively when randomized into the drain group. In case of splenectomy, the drain is placed such that it includes the former splenic fossa with drain openings in this area and extending its tip until next to the pancreatic transection margin while avoiding direct contact with the splenic artery/vein stumps. The placed intra-abdominal drains are passive drains and will evacuate fluid by passive gravity, without active suction.

In the drain-group amylase levels are determined on day 1, 3, and 5 postoperatively (day 0 = day of DP). The drain can be removed on day 3 unless the drain levels exceed three times the upper limit of the institutions range of serum amylase (i.e., 2016 updated ISGPS definition of pancreatic fistula) or when the amount exceeds 200ml in 24h the fluid aspect is suspicious. This stands also for those patients in the no-drain group who, despite randomization, receive a percutaneous catheter drainage for any intraoperative reasons of concern.

For other details of the surgical procedure, surgeons can use a surgical technique according to his/her own preference as long as they use the same approach in all patients. All procedure details should be recorded within the case report form.

